### 5.1 Study A

Design: Single-centre, parallel group, randomised feasibility study. This study will test the feasibility of conducting a randomised controlled trial (RCT) evaluating the psychometric impact of setting explicit glycaemic targets in people with diabetes (type 1 and type 2). There is deliberate separation of the initial clinic appointment (visit one; 0 months) and delivery of the intervention (visit two; 3 months) to allow for clinical care to be optimised and avoid conflict between the clinician advice and the study target. A short follow-up period 3 months post intervention has been selected to allow testing of feasibility outcomes and preliminary psychometric and glycaemic outcomes whilst minimising the health impact of the HbA1c target change to the participants.

Study Processes: people with diabetes meeting inclusion criteria and not excluded by exclusion criteria who are due to attend new patient diabetes clinic will be screened for entry into study A. Patients meeting eligibility criteria will be invited to entry into the study by postal letter with an included participant information sheet. Follow-up telephone calls will check patient interest and coordinate screening visits.

At visit one (0 months), invited patients will attend for a screening visit and informed consent process at the time of attendance to their diabetes clinic appointment. Those declining to take part will be

asked to complete a short survey evaluating barriers to participation (Barriers to Participation survey, [Section 11.1](#), Appendix 1). Baseline characteristics will be recorded: NHS number, age, sex, ethnicity, diabetes type, diabetes duration, postcode, point of care (POC) HbA1c, Blood Pressure (BP), BMI, educational status and prescribed glucose-lowering drugs. Participants will attend their usual diabetes clinic appointment for optimisation of their diabetes care. Participants will be randomised (stratified [strata: type 1 diabetes, type 2 diabetes]] random permuted block strategy) 1:1 into two groups using an online randomisation service (Altman and Bland, 1999, Suresh, 2011, Sealed Envelope Ltd, 2020).

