and linked through a unique study code. Separation of patient identifiers from other data will be at the point of entry into the database.

Data analysis: Participant characteristics and feasibility outcomes will be reported with descriptive statistics, presenting continuous variables as means (standard deviation, SD) and categorical variables as numbers (%). For psychometric outcomes, paired baseline and endpoint data will be presented as mean differences (95% confidence interval, p-value). The paired two-tailed student's t-test will be used to compare means of parametric datasets (EQ-VAS index scores, PAID score, SDSCA scores, DES-LF scores, WBQ-12 scores). Differences between categorical variables will be analysed using the chi-squared test (EQ-5D-5L dimension responses). The Wilcoxon rank-sum test will be used to compare non-parametric data sets (EQ-5D-5L index scores). Correlations between different psychometric outcomes will be determined using spearman's rank correlation coefficient. Statistical methods will use SPSS v.25 statistics software (IBM Corp., 2017) and expert statistician input.

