## **7.2 Sampling**

### **7.2.1 Size of sample**

Study A: Influential papers (Julious, 2005, Sim and Lewis, 2012) on the sample size requirements for feasibility studies have suggested between 24 and 50 participants are required to estimate the standard deviation of an outcome measure (often needed in the calculation of sample sizes in larger studies).

Given an estimated study participation rate of 70% of those eligible, based on participation rates of eligible patients in the DAFNE (DAFNE Study Group, 2002) and DESMOND (Davies et al., 2008) trials, 72 eligible patients will be selected for entry into the study in order to enrol 50 participants ( $70\% \times 72 \approx 50$ ).

Depending on eligibility and recruitment rates, the sample size may have to be adapted.

Study B: A stratified (by type 1 and type 2 diabetes), purposive estimated sample of 15 participants will be required. Sample adequacy will be determined using the concept of information power, described by

Malterud et al. (2016). Estimates of sample size required in similar studies suggest a requirement of 10 – 15 participants. Adjustments to sample size may be required during the study, depending on the information power of the sample.

Study C: A convenience sample of 15 participants will be recruited. Determination of sample adequacy as per study B. Adjustments to sample size may be required during the study, depending on the information power of the sample.

Study D: A stratified (by type 1 and type 2 diabetes), purposive estimated sample of 15 participants will be required. Sample adequacy will be determined as per study B. Estimates of sample size required in similar studies (Taylor et al., 2007, Harrop et al., 2016, Hughes-Morley et al., 2016) suggest a requirement of 10 – 39 participants. Adjustments to sample size may be required during the study, depending on the information power of the sample.

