*I have reviewed the protocol for the above study and have the following comments:*

This is an interesting study and protocol is generally clear and well written. I do have a few minor comments and one major comment:

CV for CI and co-investigators are missing.

Please clarify if the study is recruiting people with type 1 diabetes, type 2 diabetes or all types of diabetes. The treatment is very different and I think if all types of diabetes are being considered then it will be important to look at them separately with some stratification by diabetes type.

It is not quite clear in the protocol why targets above current HbA1c control are being used. Most patients are referred to hospital services for poor glucose control and HbA1c is often very high at point of referral. I would have preferred to have seen a modest target (5mmol/mol drop in HbA1c) vs a more stringent one (> 10mmol/mol): this would to me seem a more realistic approach. I suggest providing a stronger rationale for these higher targets or change them as suggested above. It is not quite clear to me how the usual clinicians will be providing advice that is consistent with the targets.

The HbA1c target graph in the PIS does not go down to the level of control considered adequate by many guidelines

(<53mmol/mol) - this needs to be changed to include the non-diabetic range (ie down to 48 mmol/mol and lower)

I would consider going outside a single Trust for objective C - it is likely that all the team in the St Helen's Trust will be familiar with the study, so their input may not be representative.

Date: 03/DEC/20

Signature:

[figure not shown]

[figure not shown]

ATTAINS Study. IRAS ID: 291254 Study ID: 

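### Study A is randomised by diabetes type with a pre-intervention score in hand, but its stated analysis names no A-versus-B estimate and uses neither the stratum nor the 3-month value as a covariate

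*Protocol*

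**What the plan says.** Protocol 5.1 (Study A, study processes) fixes the allocation: "Participants will be randomised (stratified [strata: type 1 diabetes, type 2 diabetes]] random permuted block strategy) 1:1 into two groups". Diabetes type is the only stratum, and it is recorded at visit 1 among the baseline characteristics: "NHS number, age, sex, ethnicity, diabetes type, diabetes duration, postcode". The questionnaires are completed at visit 2 (3 months), before the target is given, and again at visit 3 (6 months).

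The data analysis paragraph of 5.1 describes feasibility outcomes overall. For the questionnaires it says: "For psychometric outcomes, paired baseline and endpoint data will be presented as mean differences (95% confidence interval, p-value". It then assigns tests: "The paired two-tailed student's t-test will be used to compare means of parametric datasets", listing EQ-VAS, PAID, SDSCA, DES-LF and WBQ-12; a chi-squared test for the EQ-5D-5L dimensions; and "The Wilcoxon rank-sum test will be used to compare non-parametric data sets (EQ-5D-5L index scores". Spearman correlations are planned between different psychometric outcomes. Arm, diabetes type and covariates are not mentioned, and no test is assigned to HbA1c.

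Section 7.2.1 justifies the sample by literature in which 24 to 50 "participants are required to estimate the standard deviation of an outcome measure (often needed in the calculation of sample sizes in larger studies". In Appendix 1 the external peer reviewer, noting that treatment differs by type, wrote that if all types are included "it will be important to look at them separately with some stratification by diabetes type". Section 8.3 answers that point with an update to 7.1.1 and cites no analysis section.

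**The concern.** The design pays for two things that the stated analysis does not use: balance of the arms within diabetes type, and a questionnaire score taken just before the intervention. Research question 2 (section 4) asks about targets set above and below the current reading, which is a contrast between the randomised groups. A paired before-and-after difference does not answer it, whether pooled or taken within each arm.

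The second stake is the main trial. A randomised trial that adjusts for baseline is sized on the residual SD within arm, or equivalently on the outcome SD and the correlation between baseline and follow-up. The paragraph promises mean differences with CIs and p-values. It does not promise a residual SD or a 3-to-6-month correlation, and its planned correlations are between different scales.

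The peer reviewer made two requests: to stratify, and to look at the types separately. The first is met in the randomisation. Nothing in 5.1 provides for the second.

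**Working it through.** **The plan's own figure.** Section 7.2.1 needs 50 enrolled at 70% participation: 50/0.70 = 71.4, rounded up to 72, and 0.70 × 72 = 50.4. The stated 72 reproduces. The protocol gives no effect size, SD, correlation or power, so there is no precision figure to reproduce.

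**Numbers analysed.** Retention at the section 8.9 criterion is 0.80 × 50 = 40, or 20 per arm.

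**Gain from baseline adjustment.** Let ρ be the correlation of the 3- and 6-month scores, with equal SD σ at both visits. For the arm difference:

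- change score: variance proportional to 2σ²(1 − ρ)
- adjusted for the 3-month value: variance proportional to σ²(1 − ρ²)
- ratio, adjusted to change: (1 − ρ²)/[2(1 − ρ)] = (1 + ρ)/2
- narrowing of the CI: 1 − √[(1 + ρ)/2]

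| ρ (assumed) | Variance ratio | CI narrower by | Adjusted n matching 40 by change score |
|---|---|---|---|
| 0.3 | 0.65 | 19% | 26 |
| 0.5 | 0.75 | 13% | 30 |
| 0.7 | 0.85 | 8% | 34 |
| 0.8 | 0.90 | 5% | 36 |

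**Small-sample check.** These ratios ignore the cost of estimating the extra coefficients. A simulation with 20 per arm, one fifth in the smaller stratum and a 0.5 SD gap between types gave these standard errors for the arm difference (change score, then baseline plus stratum):

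- ρ = 0.5: 0.307 and 0.272, so 1 − 0.272/0.307 = 11% narrower, against 13% by formula
- ρ = 0.7: 0.245 and 0.231, so 1 − 0.231/0.245 = 6% narrower, against 8% by formula

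The gain survives at this size, about two points smaller.

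**Precision of an SD.** The 95% limits, as multiples of the estimate, are √[(n − 1)/χ²] at the 97.5% and 2.5% points. For n = 40 they are 0.82 and 1.28; for n = 10 they are 0.69 and 1.83. If one type supplies about 10 participants, its own SD is too uncertain to size a trial on. One residual SD from a model with type in it is the better target.

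**The case against.** The strongest reply is that covariates and by-stratum tables belong in an SAP, which is not shown, and that 5.1 promises statistician input. That would settle the matter if 5.1 were silent, but it assigns methods scale by scale, and for the five paired-t measures the assigned method is not an arm comparison. The reply does limit how much weight the omission carries.

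It is also fair that the study is not powered for effects and that its primary outcomes are feasibility rates. Power is therefore the wrong yardstick; CI width and the planning SD are the relevant ones. For the overall before-and-after change, which is what 5.1 names, baseline adjustment brings no comparable gain. The figures above apply only once an arm estimate is added.

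Three stronger readings are tempting, and the documents do not support them.

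- **That mixing the types inflates the main-trial sample size.** With 30% type 1 and gaps of 0.5, 1.0 or 1.5 within-type SDs, a raw single-visit variance rises by v = 0.3 × 0.7 × gap² = 5%, 21% or 47%. Section 5.1 plans paired differences, in which a constant gap cancels: the variance stays at 2(1 − ρ), or 1.00 at ρ = 0.5, for every gap. In a baseline-adjusted model that omits type, the residual variance at ρ = 0.5 is (1 + v) − (0.5 + v)²/(1 + v) = 0.76, 0.79 or 0.83 against 0.75, an excess of roughly 2%, 6% or 11%. Nothing says a raw pooled SD will size the main trial.
- **That a pooled green verdict is unsound without a by-type condition.** Retention of 40/50 could hide 7/12 in one type and 33/38 in the other, but that split is invented and the exact 95% CI for 7/12 (28% to 85%) includes 80%. Pooling does not bias the overall rates; it only withholds the breakdown.
- **That baseline is used only by subtraction throughout.** The EQ-5D-5L index has a rank-sum test and the dimensions a chi-squared test, neither of which subtracts anything. Both could be meant as arm comparisons, but the paragraph does not say what groups are compared.

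**Conclusion.** The point holds in this form: the stated Study A analysis names no estimate of the difference between the randomised groups, leaves out the only stratification factor, and does not use the 3-month score as a covariate. The missing arm estimate is the larger part; adjustment is the right way to supply it.

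The size is modest: an interval about 19% to 5% narrower than with change scores for correlations of 0.3 to 0.8, and about two points less at the correlations simulated with 20 per arm. That rests on an assumed correlation and equal SDs at the two visits. It also assumes that the 3-month score is unaffected by allocation. Randomisation is at visit 1, but the script in Appendix 1 places the questionnaires before the target is given. By-type reporting of feasibility is worth having as description and supports no separate progression threshold.

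**What to change.** In section 5.1, data analysis:

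1. For each continuous psychometric score and for HbA1c, estimate the group A minus group B difference with a 95% CI from a linear model of the 6-month value on arm, 3-month value and diabetes type.
2. Report the residual SD from that model and the 3-to-6-month correlation of each outcome, as inputs to the main-trial sample size.
3. Tabulate eligibility, recruitment, retention, response and acceptability by diabetes type beside the total, with CIs, as description only. Section 8.9 needs no by-type threshold.

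This is a change of wording that uses data already planned. It costs one or two degrees of freedom, and the figures for the smaller type will be imprecise and should be labelled so.

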### 4 RESEARCH QUESTION/AIM(S)

1. What is the feasibility of undertaking a randomised control trial evaluating the effect of setting explicit glycaemic targets on psychometric and glycaemic outcomes in people with diabetes? **(Study A)**
2. What is the preliminary impact of setting explicit glycaemic targets above and below current HbA1c readings on psychometric and glycaemic outcomes in people with diabetes? **(Study A)**
3. What are the experiences, views and opinions of people with diabetes on the acceptability of the study processes and on glycaemic target-setting? **(Study B)**

4. What are the experiences, views and opinions of healthcare professionals on glycaemic target-setting and on the use of individualised treatment targets in people with diabetes? (**Study C**)
5. What are the experiences, views and opinions of people declining entry into study A on barriers to participation in diabetes research? (**Study D**)

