At visit two (3 months), participants will visit to have a POC HbA1c reading and complete a series of validated baseline psychometric questionnaires (EQ-5D-5L – Health-related quality of life measure, SDSCA – Summary of Diabetes Self-Care Activities, PAID – Problem Areas in Diabetes, DES-LF – Diabetes Empowerment Scale, WBQ-12 – Well-being Questionnaire). The study intervention will be delivered as described using the TIDieR Checklist (Hoffmann et al., 2014):

- Intervention: Participants in group A are given an explicit HbA1c target 5mmol/mol above their current HbA1c reading. Participants in group B are given an explicit HbA1c target 5mmol/mol below their current HbA1c reading.
- Rationale: The feasibility of studying the use of glycaemic target-setting on psychometric outcomes in people with diabetes is unknown. Over-achievement and under-achievement of glycaemic targets has an unknown effect on psychometric outcomes and long term glycaemic control in people with diabetes.
- Materials: Participants will be provided with a sterilised, laminated leaflet (see Appendix 2) explaining in lay terms the rationale for HbA1c monitoring in diabetes. The leaflet will include a diagrammatic representation of their current HbA1c reading against their explicit target. A short scripted HbA1c summary will be read to participants by the researcher, along with an opportunity for participants to ask questions.
- Intervention provider: the intervention will be provided by the researcher employed by St Helens and Knowsley Teaching Hospitals NHS Trust. The researcher has a background working as a specialist trainee in diabetes and endocrinology and is fully trained in infection control measures, including precautions related to COVID-19.
- Mode of intervention delivery: the intervention will be provided face-to-face on an individual basis, following the latest UK government guidance on personal protective equipment and social distancing.
- Location: the intervention will be in a consultation room in the Diabetes Centre in St Helens Hospital.
- Time requirements/timing: the intervention will take place 3 months after study entry to allow for initial secondary care clinical management (undertaken at study entry) to be fully

established. Patients will attend the Diabetes Centre to complete a series of baseline questionnaires (30 minutes), a blood sample (10 minutes) and the intervention (5 minutes).

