#### 9. Risk of research intervention.

Pre-mitigation risk:

Severity: 1. Likelihood: 3. Risk: 3 (Low)

Mitigation:

The research intervention is to set an explicit A1c target for the patient. It is common for patients to be set glycaemic targets as part of secondary care diabetes clinic procedures. Higher A1c targets could result in participants relaxing their glycaemic control. Lower A1c targets could result in participants tightening their glycaemic control. Their clinical management by a senior diabetes clinician will remain unchanged. By taking part in the feasibility study, the participants will have the benefit of two visits to see a diabetes clinician where they would commonly be seen only once. At the patient's last clinic visit, an appropriate A1c will be discussed with them to enable optimisation of their management following completion of the study.

Risk rationale:

The patient will have a study-set A1c target for only three months. Whether their target is set above or below their current A1c reading, the three-month window of A1c target alteration would be unlikely to have any impact on the patient's physical health.

Post-mitigation risk:

Severity: 1. Likelihood: 3. Risk: 3 (Low)

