#### Study A:

##### *Data type and format*

Biochemical (finger-prick blood test: HbA1c in mmol/mol), physiological (blood pressure in mmHg, Body Mass Index in kg/m^2) and baseline demographic (age, gender, ethnicity, diabetes type, diabetes duration, GP practice, postcode, educational status, prescriptions) data from a pragmatic sample of 100 randomly selected participants due to attend diabetes clinic at St Helens Hospital in the Northwest UK will be obtained at recruitment (baseline), 3 months and 6 months (endpoint).

Patient-reported outcome data (validated, self-completed, paper questionnaires) will be recorded from the same population at 3 months and 6 months. Biochemical, physiological and demographic data will be recorded in a password-protected Excel database (.xlsx) and analysed using SPSS (.sav). Questionnaire scores will be recorded in a password-protected excel database and analysed using SPSS.

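### Study A's analysis paragraph gives the paired change as its only effect measure and names no comparison of group A with group B, so it does not estimate the above-versus-below effect for which the study randomises

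*Protocol*

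**What the plan says.** Protocol Section 5.1 describes Study A as a "Single-centre, parallel group, randomised feasibility study", with allocation "1:1 into two groups using an online randomisation service", stratified by type 1 and type 2 diabetes. The contrast is fixed: "Participants in group A are given an explicit HbA1c target 5mmol/mol above their current HbA1c reading", and group B receives one 5 mmol/mol below. Section 2 (Rationale) gives the reason for having both directions: to test whether over- and under-achieving a target differ in their psychological effect. Research question 2 in Section 4 asks: "What is the preliminary impact of setting explicit glycaemic targets above and below current HbA1c readings", for psychometric and glycaemic outcomes alike.

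The Data analysis paragraph of Section 5.1 then states: "For psychometric outcomes, paired baseline and endpoint data will be presented as mean differences (95% confidence interval, p-value". It assigns tests as follows:

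- **Paired two-tailed t-test:** EQ-VAS, PAID, SDSCA, DES-LF and WBQ-12.
- **Wilcoxon rank-sum test:** EQ-5D-5L index.
- **Chi-squared test:** EQ-5D-5L dimension responses.
- **Spearman correlation:** between the psychometric outcomes.

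The paragraph mentions neither group A nor group B, no difference between them, and not diabetes type. HbA1c change is listed as a preliminary outcome in Section 4.2, but no comparison is given for it.

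**The concern.** A paired test asks whether scores moved between 3 and 6 months. Research question 2 and the Rationale ask whether the two targets differ in effect, and only a comparison of the arms answers that. The paragraph also does not say whether the paired tests pool the arms or run within each arm, and both readings fail. A pooled test averages over the two targets, so it hides effects in opposite directions, which is the pattern the Rationale sets out to detect. Separate within-arm tests invite the conclusion that one target changed well-being and the other did not, from two p-values on either side of 0.05. Neither arm is without a target, so a within-arm change also cannot be separated from a trend over time. The unpaired tests leave a further ambiguity: they could be between-arm comparisons, or they could be applied to baseline and endpoint scores from the same people, where they would be the wrong tests.

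**Working it through.** **Plan's own figure.** Section 7.2.1 states 70% × 72 ≈ 50. Check: 0.70 × 72 = 50.4, and 50/0.70 = 71.4, rounded up to 72. It reproduces. The protocol gives no effect size, SD or power for the psychometric scores, so there is no power figure to reproduce.

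**Inputs from the protocol.** N = 50 allocated 1:1 gives 25 per arm. The retention criterion of at least 80% (Section 8.9) gives 0.80 × 50 = 40, or 20 per arm. Tests are two-sided. I take 0.05 as the significance level.

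**Assumed inputs.** The documents give no SD, correlation between the 3- and 6-month scores, or expected shift. I use a correlation ρ = 0.6 and a shift of 0.3 to 0.4 SD, varied below.

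**1. Separate within-arm tests, same shift in both arms, no target effect.**
Standardised paired effect: d_z = shift / √(2(1 − ρ)). With n = 20, the noncentrality is d_z√n on 19 degrees of freedom. If each test has power p, exactly one arm is significant with probability 2p(1 − p).
- Shift 0.4: d_z = 0.4/√0.8 = 0.447; p = 0.476; 2 × 0.476 × 0.524 = 0.499.
- Shift 0.3: d_z = 0.3/√0.8 = 0.335; p = 0.297; 2 × 0.297 × 0.703 = 0.417 (from unrounded p).

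The same formula over a wider range of assumptions, n = 20 per arm:

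| ρ | Shift 0.3 SD | Shift 0.4 SD |
|---|---|---|
| 0.5 | 0.37 | 0.48 |
| 0.6 | 0.42 | 0.50 |
| 0.7 | 0.47 | 0.48 |

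With no shift in either arm, the simulated figure is 9.5% (2 × 0.05 × 0.95 = 0.095). The problem therefore needs some common movement over time. A between-arm t-test on the changes rejects in about 5% of trials whatever the common shift.

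**2. Pooled paired test, opposite changes.** With true changes of +0.5 and −0.5 (in units of the SD of change) and equal arms, the expected pooled change is (0.5 − 0.5)/2 = 0. Simulation with 40,000 replicates:

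| Per arm | Pooled paired test rejects | Between-arm t-test rejects |
|---|---|---|
| 20 | 2.7% | 87% |
| 25 | 3.0% | 93% |

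**3. Rank-sum test on paired data.** If the EQ-5D-5L index were compared between baseline and endpoint with the rank-sum test, the pairing would be ignored. Simulated null rejection (n = 20, 4,000 replicates) is 0.8% at ρ = 0.5 and 0.1% at ρ = 0.7, against a nominal 5%.

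**4. What the planned data can give.** The 95% CI half-width for a between-arm difference in mean change, in units of the SD of change, is t(0.975, 2n − 2) × √(2/n).
- 25 per arm: 2.011 × √0.08 = 0.57.
- 20 per arm: 2.024 × √0.10 = 0.64.

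Power for a 0.5 SD difference is 42% (25 per arm) or 35% (20 per arm). The estimate is available but imprecise, which suits a preliminary aim and rules out an efficacy claim.

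**The case against.** The best defence is that this is a feasibility study. All primary outcomes in Section 4.2 are feasibility measures, to be reported descriptively. Psychometric and HbA1c changes are labelled preliminary, and no psychometric result enters the progression criteria in Section 8.9. Model details such as covariates are commonly left to an SAP, which is not shown here. This stands, and it limits how serious the point is. It does not remove it, because the protocol does not leave the effect measure open: it fixes a paired change, and an SAP that follows it inherits the mismatch with research question 2.

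A reader might infer more than the documents support:

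- **That every planned test is paired.** The rank-sum and chi-squared tests are for independent samples and may be an unlabelled between-arm comparison. The text does not settle this.
- **That the study cannot estimate the effect.** Both arms are measured at 3 and 6 months, so it can. The stated analysis simply does not.
- **That the added clinic visit explains within-arm change.** The risk section says "the participants will have the benefit of two visits to see a diabetes clinician where they would commonly be seen only once". By the schedule in Section 5.1, clinic appointments fall at 0 and 6 months, the latter at the same visit as the endpoint, so it cannot drive the 3-to-6-month HbA1c change. Initial optimisation is deliberately placed before the 3-month reading.
- **That HbA1c change will be counted from recruitment.** The data management plan says data "will be obtained at recruitment (baseline), 3 months and 6 months (endpoint". That labels collection times. Section 4.2 identifies the 3-month reading as the one before the intervention, and no passage plans to attribute the 0-to-6-month change to the target.
- **That the sample-size purpose is defeated.** Section 7.2.1 says cited papers "suggested between 24 and 50 participants are required to estimate the standard deviation of an outcome measure". A paired mean difference with its CI and n already yields an SD of change.

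**Conclusion.** The point holds as a mismatch between the randomised question and the stated analysis. The Study A paragraph gives paired change as its only effect measure, names no comparison of the arms for the five t-tested instruments or HbA1c, and does not say what its two unpaired tests compare. Followed literally, it would mask opposite effects or make exactly one arm significant in about 42–50% of trials with no target effect. That range rests on 20 completers per arm, a correlation of 0.6 and a common shift of 0.3–0.4 SD. Correlations of 0.5 to 0.7 widen it to about 37–50%, and with no common shift it falls to about 10%. Only the preliminary aim (research question 2) is affected, so the correction is well worth making but does not threaten the study's primary purpose.

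**What to change.** Rewrite the Data analysis paragraph of Section 5.1:

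1. For each questionnaire score and for HbA1c, report the between-arm difference at 6 months with a 95% CI from ANCOVA, adjusting for the visit 2 (3-month) value and for diabetes type, the randomisation stratum. Label it a preliminary estimate with no claim of efficacy.
2. Report within-arm changes descriptively, without p-values.
3. State that any rank-sum or chi-squared test compares group A with group B, not baseline with endpoint.

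The cost is one reworded paragraph. No extra participants, visits or measurements are needed, and the SPSS version already named can fit the model.

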**MOBILITY**

- I have no problems in walking about ☐
- I have slight problems in walking about ☐
- I have moderate problems in walking about ☐
- I have severe problems in walking about ☐
- I am unable to walk about ☐

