**ANXIETY / DEPRESSION**

- I am not anxious or depressed ☐
- I am slightly anxious or depressed ☐
- I am moderately anxious or depressed ☐
- I am severely anxious or depressed ☐
- I am extremely anxious or depressed ☐

- We would like to know how good or bad your health is TODAY.
- This scale is numbered from 0 to 100.
- 100 means the best health you can imagine.  
0 means the worst health you can imagine.
- Mark an X on the scale to indicate how your health is TODAY.
- Now, please write the number you marked on the scale in the box below.

YOUR HEALTH TODAY =

The best health  
you can imagine

[figure not shown]

The worst health  
you can imagine

Date: \_\_\_\_\_  
**Date:** \_\_\_\_\_

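### The ordered EQ-5D-5L dimension responses are assigned an ordinary chi-squared test, which ignores severity order and, if the comparison is month 3 v month 6, also ignores pairing

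*Protocol*

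**What the plan says.** Section 5.1 of the protocol (Study A, Data analysis) names both the test and the variable: "Differences between categorical variables will be analysed using the chi-squared test (EQ-5D-5L dimension responses". It mentions no trend or ordinal version.

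The questionnaire in Appendix 1 shows that every dimension is a severity ladder from no problems, through slight, moderate and severe, to unable or extreme. Two of the middle steps read "I have slight problems in walking about" (mobility) and "I am moderately anxious or depressed" (anxiety/depression).

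The same paragraph treats the summary of these five items differently: "The Wilcoxon rank-sum test will be used to compare non-parametric data sets (EQ-5D-5L index scores". It introduces the psychometric analysis as within-person: "For psychometric outcomes, paired baseline and endpoint data will be presented as mean differences (95% confidence interval, p-value". No test of group A against group B is stated.

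On size, section 7.2.1 says "72 eligible patients will be selected for entry into the study in order to enrol 50 participants". Section 4.2 lists psychometric change among the other (preliminary) outcomes.

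**The concern.** The chi-squared statistic adds up squared discrepancies over cells. The position of a column on the severity scale does not enter, so a steady movement towards worse levels and an arbitrary reshuffle of the same columns give the same p-value. The test also spends four degrees of freedom on what is usually a one-directional question, and it reports neither direction nor size.

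Research question 2 (section 4) asks for the preliminary impact of targets above and below current HbA1c, where direction matters. The index score, built from these same responses, gets a method that uses order, while the components do not.

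The comparison itself is also unclear. The paragraph opens with paired data, yet rank-sum and ordinary chi-squared are both tests for independent samples. If the dimensions are compared between month 3 and month 6 in the same people, chi-squared breaks its independence assumption as well as discarding order.

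**Working it through.** **1. Numbers available.** The plan's own figure reproduces: 0.70 × 72 = 50.4, about 50 enrolled. With 1:1 allocation (section 5.1) that is 25 per arm. The section 8.9 thresholds give 0.80 × 50 = 40, or 20 per arm (retention), and 0.60 × 50 = 30, or 15 per arm (questionnaire response).

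**2. Assumptions.** The protocol states no alpha, EQ-5D effect or distribution. Assumed here:
- two-sided 5%, in line with the protocol's 95% intervals ("mean differences (95% confidence interval, p-value") and its two-tailed t-test ("The paired two-tailed student's t-test will be used to compare means of parametric datasets");
- reference levels 35/27/22/11/5%;
- a proportional-odds shift.

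At OR 3 the probabilities of exceeding levels 1 to 4 are:
- 3×0.65/(0.35+3×0.65) = 0.848
- 3×0.38/(0.62+3×0.38) = 0.648
- 3×0.16/(0.84+3×0.16) = 0.364
- 3×0.05/(0.95+3×0.05) = 0.136

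The shifted levels are therefore about 15/20/28/23/14%.

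**3. One illustrative table.** Multiplying by 25 and rounding to totals of 25 gives 9/7/5/3/1 against 4/5/7/6/3.
- Chi-squared with equal arms is Σ(a−b)²/(a+b) = 25/13 + 4/12 + 4/12 + 9/9 + 4/4 = 4.59 on 4 df, p = 0.33.
- Rank-sum: column totals 13/12/12/9/4 give midranks 7, 19.5, 31.5, 42 and 48.5. W = 531.5 against an expected 25×51/2 = 637.5. The tie-corrected variance is (625/12)×(51 − 6396/2450) = 2520. z = −106/50.2 = −2.11, p = 0.035.
- Now reorder the same columns to 5/9/3/7/1 against 7/4/6/5/3. Chi-squared is still 4.59, p = 0.33. Rank-sum gives W = 625.5, z = −12/50.2 = −0.24, p = 0.81.

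Chi-squared cannot tell the consistent shift from the reshuffle; the rank test can.

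**4. Power between arms** (simulated; Pearson chi-squared with empty columns dropped v tie-corrected rank-sum).

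| Per arm | OR | Chi-squared | Rank-sum | Gain (points) |
|---|---|---|---|---|
| 25 | 1.5 | 7.6% | 12.7% | 5 |
| 25 | 2 | 14% | 27% | 13 |
| 25 | 3 | 33% | 55% | 22 |
| 25 | 4 | 51% | 76% | 25 |
| 20 | 2 | 11% | 21% | 10 |
| 20 | 3 | 25% | 47% | 22 |
| 20 | 4 | 41% | 66% | 25 |
| 15 | 2 | 8% | 16% | 8 |

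Monte Carlo error is at most √(0.25/3000) = 0.9 points per entry. Over repeated runs at 15, 20 and 25 per arm the gain is about 3-5 points at OR 1.5, 9-14 at OR 2 and 16-24 at OR 3-4; table entries one point outside these ranges are within that error.

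**5. Power on the paired reading** (ordinary chi-squared v signed-rank; latent correlation 0.5 or 0.7; levels here 35/25/20/15/5%; 3,000 replicates).

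| Pairs | Correlation | Shift 0.3 SD | Shift 0.5 SD |
|---|---|---|---|
| 25 | 0.5 | 6% v 24% | 12% v 53% |
| 25 | 0.7 | 4% v 31% | 10% v 69% |
| 40 | 0.5 | 7% v 32% | 24% v 73% |
| 40 | 0.7 | 5% v 50% | 21% v 89% |
| 50 | 0.5 | 10% v 44% | 32% v 84% |
| 50 | 0.7 | 8% v 58% | 28% v 94% |

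With no shift, chi-squared rejects about 1-3% of the time instead of 5%. Under the reference levels of step 2 the loss is roughly 17-69 points. With 20 pairs and a more skewed distribution the lower end falls to 12.

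This loss mixes ignored pairing with ignored order. A paired nominal test (Stuart-Maxwell) still trails signed-rank: 23-84% v 46-98% with 50 pairs, and 17-72% v 37-93% with 40. Part of that gap is its own conservatism (null rejection 2.8-3.4%).

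**6. Sparse cells.** With 25 per arm at the reference levels, the expected counts in the top two levels are 25×0.11 = 2.75 and 25×0.05 = 1.25, so two of five columns fall below 5. Simulated null rejection between arms was nevertheless 4.0-4.1%, so the approximation is only mildly conservative.

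**The case against.** The strongest reply is that little depends on this p-value. The primary outcomes are eligibility, recruitment, retention, response and acceptability. The sample was sized to estimate a standard deviation, and no EQ-5D result enters the green/amber/red criteria in section 8.9. Psychological effect is also captured by PAID and WBQ-12, analysed as scores, and EQ-5D-5L has an index and a VAS with their own tests. All of this stands, and it limits the consequence.

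Three stronger readings are tempting, and the documents support none of them:
- A reader might infer a fixed loss of 10 to 30 points of power. No such figure follows from the protocol. It depends on an assumed effect of about OR 2 or more and on a between-arm comparison that section 5.1 does not state. At OR 1.5 the loss is about 3-5 points.
- A reader might infer that sparse cells invalidate the test. Null rejection of about 4% does not bear that out.
- A reader might infer that any Wilcoxon test repairs the report. A Wilcoxon p-value alone gives no effect size, and a proportional-odds model with covariates may be unstable in 40 to 50 people.

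The objection does not remove the mismatch. The protocol itself pairs this test with this variable, so the choice has not been left open for a later analysis plan.

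**Conclusion.** The concern holds in a limited form. The named test ignores the order of a five-level severity scale, so it is less sensitive to a consistent shift than a rank test on the same data. That statement needs no assumption about the data beyond the shift being consistent.

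The size of the loss is conditional: modest for small between-arm shifts, substantial for large ones, and largest on the paired reading, where two faults combine. At OR 3 the proportion with no problems falls from 35% to 15%, so the upper figures describe large effects.

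The result is a less informative preliminary finding on one instrument. It is no threat to the feasibility conclusions or to progression. It is worth correcting because the correction is nearly free.

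**What to change.** In section 5.1:

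1. State whether the EQ-5D-5L dimensions are compared within person (month 3 v month 6), between groups A and B at month 6, or both.
2. Replace chi-squared for these responses with the Wilcoxon signed-rank test for the within-group comparison and/or the Wilcoxon rank-sum test for the between-group comparison.
3. Report a rank-based effect size, such as the probability of superiority, with its 95% CI.
4. Keep n (%) by level as description, and reserve chi-squared for truly nominal variables. A proportional-odds model is optional, with a caution about stability at this sample size.

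The cost is a sentence or two of protocol text. No extra data, visits or participants are needed, and the paragraph already plans a Wilcoxon test.
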